### Blinding

Blinding of subjects and interveners is not feasible due to the inclusion of exercise and acupuncture interventions in this study. However, assessors will remain blinded. All participants and assessors will receive strict instructions not to discuss or disclose any information regarding the intervention methods prior to the start of assessments. Independent research personnel will be present at all times to ensure successful blinding procedures are maintained consistently throughout data collection processes. In cases where assessors become aware of a subject’s intervention method during assessment, their involvement will be terminated promptly with replacement by another assessor.

### Interventions

#### Control group

CG will receive usual medical care in accordance with the international guidelines (42, 43), and health education every 2 weeks, covering the concept, risk factors, and self-management of COPD. During the trial, the patients will be asked to maintain their extant daily habits, and regular weekly telephone calls will be conducted to ask them about their medications, exercise, and daily activity for the week to ensure adherence to the trial.

#### PQ exercise group

PQG will receive an 8-week intervention of PQ exercise (44), three times per week for 60 min per session (Figure 2). Two weeks before the intervention, a coach with more than 20 years of Qigong experience will train and assess the three researchers who are responsible for teaching the participants to ensure that these researchers master all the points of Qigong. During the intervention period, exercise groups consisting of 6–12 patients will be formed, and each group will receive step-by-step instructions from the three researchers. The training sessions will comprise three 1-h sessions per week, totaling 24 sessions, of which the training structure includes warm-up, core activities, and cooldown. In 1–6 training sessions, the patients will be systematically taught to master all the points of Qigong. In 7–24 training sessions, the patients will practice PQ exercises together with the researchers. Further details regarding the intervention protocol can be found in Supplementary File 2. The attendance required is no less than 85%. The training load will be monitored using the Borg CR10 scale at a level of 4–6 (42). If a subject cannot perform a specific exercise at the right intensity, he or she could perform at best achieved intensity, and the researchers will record the performance. If the subjects feel tired during the training, they could take a break and continue to complete the training. The exercise place is an independent and spacious place with suitable temperature and good ventilation. It could accommodate more than 20 people, and it is equipped with effective first-aid facilities.

**Figure 2 fig2:**
[figure not shown]
Demonstration of pulmonary-based Qigong exercise. The figure is a schematic diagram of nine actions, mainly including movements of the body and limbs, rhythm of exhalation and inhalation, and the direction of eye observation. **(A)** Rise-up position; **(B)** “Hu” sounding; **(C)** “Si” sounding; **(D)** Pushing up the sky to regulate the triple warmer; **(E)** Drawing a bow to shoot a vulture; **(F)** Crane extension in the crane exercise; **(G)** Crane fly in the crane exercise; **(H)** Cross-armed iron staff; **(I)** Restore position.

#### Acupuncture group

AG will receive an 8-week intervention of acupuncture therapy, three times per week, for 20 min per session (Figure 3). The selected acupoints are Lieque (LU7), Dingchuan (EX-B1), Feishu (BL13), Pishu (BL20), Shenshu (BL23), Zusanli (ST36), and Fenglong (ST40). The acupoints are selected bilaterally. The location of acupoints and the direction and depth of needle insertion are shown in Table 2 (45, 46). Treatment will be performed by a licensed acupuncturists who have at least 3 years of experience with acupuncture. The disposable sterile acupuncture needles of Huatuo brand are selected, with specifications of 0.3 × 40 mm and 0.3 × 25 mm. The acupuncturist will instruct the patient to assume a seated position and proceed to sterilize the targeted area by using sterile tweezers and a cotton ball soaked in 75% alcohol, followed by performing acupuncture techniques to ensure the attainment of “*de qi*” sensation (a composite of sensations including soreness, numbness, distention, heaviness, and other sensations), which is considered an important element in the efficacy of acupuncture (47). Then, an electroacupuncture device (SDZ-III, Huatuo, China) with a frequency of 2 Hz and continuous wave will be attached to the needle handles at the bilateral BL20 and EX-B1, ST36 and ST40, respectively, forming four circuits. The patients will be instructed to refrain from drinking alcohol, strong tea, coffee, high-intensity exercise, and over-hunger and to remain calm before treatment. The acupuncture site is far away from the exercise site, and it is an independent place with suitable temperature and safe environment, equipped with effective first-aid facilities.

**Figure 3 fig3:**
[figure not shown]
Details of acupuncture therapy. The red mark indicates the acupoint and connection mode of electroacupuncture.

**Table 2 tab2:** Location of acupoints and direction and depth of needle insertion.

Acupoint	Area	Location	Needle insertion
Lieque (LU7)	Lateral forearm	In the depression of the abductor pollicis longus tendon groove between the extensor pollicis brevis tendon and abductor pollicis longus tendon, which is 1.5 cun above the transverse line of the distal carpal volar.	Angled upward, 0.3–0.5 cun.
Dingchuan (EX-B1)	Cervical region	0.5 cun horizontally next to the depression below the spinous process of the 7th cervical spine.	Vertically or slightly inward, 0.5–1 cun.
Feishu (BL13)	Dorsal region	1.5 cun horizontally next to the depression below the spinous process of the 3rd thoracic vertebra.	Lateral inclination of 45 degrees, 0.5–1 cun.
Pishu(BL20)	Dorsal region	1.5 cun horizontally next to the depression below the spinous process of the 11th thoracic vertebra.	Vertically, 0.5–1 cun.
Shenshu (BL23)	Lumbar region	1.5 cun horizontally next to the depression below the spinous process of the 2nd lumbar spine.	Vertically, 0.5–1 cun.
Zusanli (ST36)	Lateral calf region	3 cun below the Dubi (ST35) on the line between Dubi (ST35) and Jiexi (ST41). Note: ST35 is located in the depression on the lateral side of the patellar ligament in the anterior region of the knee; ST41 is located in the depression in front of the ankle joint between the extensor pollicis longus tendon and the extensor digitorum longus tendon.	Vertically, 1–2 cun.
Fenglong (ST40)	Lateral calf region	8 cun above the tip of the lateral malleolus, lateral margin of the tibialis anterior muscle, 1 cun outside the Tiaokou (ST38). Note: ST38 is 8 cun below ST35 on the lateral side of the calf and on the line between ST35 and ST41.	Vertically, 1–1.5 cun.

Cun is the unit of length. In this paper, the width of the interphalangeal joint of the patient’s thumb is 1 cun. When the second to fifth fingers of the patient are closed, the width of the four fingers is 3 cun based on the transverse lines of the proximal interphalangeal joint of the middle finger.

#### PQ exercise and acupuncture combined group

PAG will receive an 8-week intervention of PQ exercise combined with acupuncture therapy three times per week for 80 min per session. The time between the two treatments will be at least 1 h to ensure that the patients are well rested and in good condition.

### Outcome measures

#### Primary outcome

The primary objective of this study is to evaluate the change in exercise endurance after an 8-week intervention. Exercise endurance will be assessed by 6MWT. In accordance with the American Thoracic Society guidelines for 6MWT, a closed, long, straight, flat corridor in the room will be selected; a 30-meter scale will be placed on the ground; and the starting points of both ends will be marked with bright color bands. The patients will be asked to walk back and forth as fast as they could within 6 min, and the maximum distance walked will be recorded as 6MWD (48).

#### Secondary outcomes

Lung function will be assessed using a spirometer (MasterScreen-Body/Diff, CareFusion Germany 234 GmbH, Germany) by a professional technician in accordance with the American Thoracic Society/European Respiratory Society guidelines (49). The outcomes include forced vital capacity, forced expiratory volume in 1 s/forced vital capacity (FEV1/FVC), predicted FEV1% (FEV1%pred), forced expiratory flow at 25% of forced vital capacity predicted (FEF25%), FEF50%, FEF75%, and maximum mid-expiratory flow after bronchodilator inhalation.The degree of dyspnea in patients will be measured using the modified Medical Research Council Dyspnea Scale, which is a 5-point scale (0–4) on which higher scores indicate worse levels of dyspnea (42).Diaphragmatic function will be evaluated by a color Doppler ultrasonic diagnostic apparatus (Aplio i900TUS-AI900, Canon, Japan) with a linear array probe (10–18 MHZ, i18LX5) in M-mode. Two experienced and trained sonographers will perform the procedure. First, the sonographer will instruct the patients to assume a seated position and place the probe at the junction of the right anterior axillary line and the 7th–9th intercostal space, ensuring that the sampling line is perpendicular to the diaphragm (50). Subsequently, precise adjustments will be made for each individual to optimize visualization of dynamic diaphragmatic images. Finally, clear and stable recordings of dynamic diaphragmatic images under resting breathing will be obtained. The diaphragm thickness at end-expiration and end-inspiration (the distance between the parallel hyperechoic medial sides of the diaphragm) and the contraction velocity of the diaphragm (displacement/time) will be measured and recorded by the sonographer. The measurements will be repeated three times, and the average value will be taken. Besides, the diaphragm thickening ratio ((mean thickness at end-inspiration – mean thickness at end-expiration)/mean thickness at end-expiration) will be calculated and recorded.The maximal inspiratory pressure (MIP) and maximal expiratory pressure (MEP) of respiratory muscle strength will be measured using a respiratory muscle strength tester (TA1, BreathHome, China). The patients will be asked to use a mouthpiece to ensure no air leakage in the mouth and nose. After breathing stably, the patients will be asked to inhale hard and quickly for more than 3 s, and the MIP will be automatically calculated by the software. After breathing stably, the patients will exhale hard and quickly for more than 3 s, and the MEP will be automatically calculated by the software. The measurements will be repeated three times with a 1-min rest interval to take the best value.Skeletal muscle structure will be measured by a color Doppler ultrasonic diagnostic apparatus (Aplio i900TUS-AI900, Canon, Japan) with a linear array probe (10–18 MHZ, i18LX5) in M-mode. First, The patients will be asked to lie in a supine position, breathe calmly, with their upper limbs extended and palms up and naturally placed at the side of the body. The probe will be placed at the middle and upper 1/3–1/2 of the starting and end points of the biceps brachii muscle to collect clear and stable images. The thickness of the soft tissue in front of the humerus and the cross-sectional area of the biceps brachii muscle will be calculated and recorded. Second, the probe will be placed at 1/2–3/5 of the distance from the anterior superior iliac spine to the upper edge of the patella to collect clear and stable images of the patient in supine position while the lower limb is extended. The thickness of the soft tissue in front of the femur and the cross-sectional area of the rectus femoris muscle will be calculated and recorded. All the above tests will be repeated three times, and the average value will be taken.Skeletal muscle function will be assessed using an isokinetic muscle strength testing system (HUMAC NORM, CSMi, American) and a wireless bio-signal acquisition system (Delsys Inc., Boston, United States) to evaluate the strength and endurance of the major skeletal muscles of the upper and lower limbs. Isokinetic muscle strength tests will be performed at slow (60°/s) and fast (180°/s) angular velocities on the elbow and knee joints separately by a technician in accordance with the manual of the instrument. At an angular velocity of 60°/second, the patients will be instructed to perform five consecutive flexion and extension exercises with their maximum effort within the designated range of motion, and peak torque will be recorded. At an angular velocity of 180°/second, the patients will be asked to complete 30 consecutive flexion and extension exercises with their maximum effort throughout the entire range of motion, and total work and fatigue index are recorded. Moreover, surface electromyography signals from two 6-s maximal static contraction tests and one exhaustive static contraction test will be collected for analysis to measure the root mean square, median frequency, and mean power frequency.The psychological states of the participants will be evaluated using the Hamilton Anxiety Scale (HAMA) and the Hamilton Depression Scale (HAMD), which will be completed through self-assessment (51). The HAMA, consisting of 24 items scored from 0 to 4, will assess anxiety symptoms. The HAMD, consisting of 24 items rated on a scale of 0–2 or 0–4, will evaluate depressive symptoms. Higher scores indicate higher levels of anxiety and depression.QoL will be assessed utilizing the St. George’s Respiratory Questionnaire, a specific assessment tool for patients with COPD (52). This questionnaire comprises a total of 50 questions that cover three main aspects: symptoms, activities, and effect on daily activities. Each question is scored on a scale ranging from 0 to 100 on the basis of its significance, with lower scores indicating no impairment and higher scores indicating extreme impairment.The frequency and severity of AECOPD 1 year before and after the intervention will be recorded.

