### Study design

This study is a single-center, assessor-blinded, data analyst-blinded, four-arm randomized controlled trial to be conducted at Shuguang Hospital Affiliated to Shanghai University of Traditional Chinese Medicine (TCM) in accordance with the Consolidated Standards of Reporting Trials (CONSORT) 2010 statement and the Standards for Reporting Interventions in Clinical Trials of Acupuncture (STRICTA) criteria (38, 39). A total of 132 participants will be recruited between October 2023 and October 2024, and randomly allocated to PQ exercise group (PQG), acupuncture group (AG), PQ exercise and acupuncture combined group (PAG), or control group (CG) at a 1:1:1:1 ratio. All participants will receive usual medical care and health education; those in the three intervention groups will receive PQ exercise, acupuncture treatment, or a combination of both treatments three times per week for 8 weeks. The primary outcome will be exercise endurance as assessed by a 6-min walk test (6MWT). Secondary outcomes will include lung function, degree of dyspnea, diaphragmatic function, respiratory muscle strength, skeletal muscle structure, skeletal muscle function, psychological states, and QoL. Exploratory outcomes will include the levels of inflammatory mediators. Outcomes will be measured within 1 week before and after the interventions. In addition, the frequency and severity of acute exacerbation of COPD (AECOPD) will be recorded at baseline and 1 year after intervention. A flow diagram of the study design is shown in Figure 1, and the study schedule is depicted in Table 1. This study has received ethics approval from Shuguang Hospital Affiliated to Shanghai University of TCM (approval number 2023–1360–127-01), and it has been registered in the Chinese Clinical Trial Registry (ChiCTR2300076255). The study protocol strictly follows the Standard Protocol Items: Recommendations for Interventional Trials (SPIRIT) checklist (Supplementary File 1).

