### Participants

Participants with confirmed COPD (42), on stable treatment for at least for 4 weeks before randomization (confirmed by absence of acute exacerbation and related drug changes), between the ages of 40 and 80 years, and who are capable and willing to provide consent are eligible to participate. The exclusion criteria are as follows: (1) coexistence of other respiratory diseases, including asthma, tuberculosis, bronchiectasis, and lung cancer; (2) severe medical condition, such as in the heart, brain, blood vessels, liver, kidneys, endocrine system, nervous system, or musculoskeletal system, that may affect exercise capacity; (3) coexistence of open injuries that are not suitable for muscle strength assessment and acupuncture treatment; (4) presence of severe speech, attention, hearing, visual, intellectual, psychiatric, or cognitive impairment that makes the individual unable to follow instructions properly; (5) women of childbearing age who were pregnant or lactating, planned to have children within 6 months, and could not take effective contraceptive measures during the trial period; (6) conditions that are not suitable for acupuncture treatment, such as dizziness, skin damage, infection, and ulcer at the acupuncture site; (7) participation in regular exercise training (at least two times per week, 60 min each time) in the past 6 months; (8) received acupuncture treatment 1 month before the trial. We will recruit potential subjects through a variety of ways, such as following up in the respiratory department of Shuguang Hospital, poster recruitment in the community service center, publicity on WeChat, and publicity in the surrounding community to reach target sample size.

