### Statistical analysis

An independent statistician who is not involved in outcome measurement will perform statistical analysis using SPSS software (version 24.0). All participants will be included in the intention-to-treat analyses. The multiple imputation method will be utilized to analyze missing data. Continuous data will be expressed as mean ± SD or median ± quartile interval, and enumeration data will be expressed as a relative ratio. Comparisons of baseline differences between groups will be performed using ANOVA or the Kruskal–Wallis H test for continuous variables and χ2 for categorical variables. Comparisons within each group (before and after 8 weeks of intervention) will be evaluated using a paired t-test or non-parametric test. Comparisons of endpoint differences between groups will be assessed using a 2 × 2 ANOVA (group × time) or the Kruskal–Wallis H test, with analysis of covariance applied when baseline is not uniform. In addition, a Difference-in-Difference (DID) analysis will be conducted to further assess the intervention effects while accounting for baseline differences and time trends.Multiple comparisons between the intervention arms will be performed using SNK-q test or the Nemenyi test. A *p* value of <0.05 will be considered statistically significant.

To further evaluate the discriminatory ability of each intervention in improving exercise tolerance, the area under the receiver operating characteristic curve (AUC) will be calculated for each intervention group, using the improvement in 6MWD as the classification criterion. Treatment effectiveness will be defined as an improvement in 6MWD ≥ 54 meters (minimal clinically important difference) (55). AUCs will be compared using the DeLong test with MedCalc software (MedCalc Software Ltd., Ostend, Belgium). A *p* value of <0.05 will be considered statistically significant.

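### Eligibility makes at least 4 weeks of the pre-intervention exacerbation year event-free, so a raw within-arm before-after AECOPD count is tilted upward by about 8% at a constant rate; the between-arm comparison is not affected

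*Protocol article*

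**What the plan says.** Four parts of the protocol article bear on this.

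- **Outcome.** Secondary outcomes: "The frequency and severity of AECOPD 1 year before and after the intervention will be recorded". Study design describes the same recording: "the frequency and severity of acute exacerbation of COPD (AECOPD) will be recorded at baseline and 1 year after intervention". Table 1 places the last AECOPD record at week 60, which is the 8 weeks of intervention plus 52.
- **Eligibility.** Participants must be "on stable treatment for at least for 4 weeks before randomization (confirmed by absence of acute exacerbation and related drug changes". The rule is the same for all four arms.
- **Within-group analysis.** Statistical analysis: "Comparisons within each group (before and after 8 weeks of intervention) will be evaluated using a paired t-test or non-parametric test".
- **Between-group analysis.** The same section states: "Comparisons of endpoint differences between groups will be assessed using a 2 × 2 ANOVA (group × time) or the Kruskal–Wallis H test". It adds that "a Difference-in-Difference (DID) analysis will be conducted to further assess the intervention effects while accounting for baseline differences and time trends".

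Statistical analysis gives one general scheme for the outcomes. It has no separate method for exacerbation counts and does not mention time at risk.

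**The concern.** The two years look like matched 52-week periods, but they are not. The eligibility rule removes events from the last 4 or more weeks of the first year, and no such rule applies to the second. A simple before-after count within an arm therefore compares a period of reduced exposure with one of full exposure.

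If such figures are reported as evidence of effect, a real reduction in exacerbations would look smaller than it is. An arm with no change, including the control arm, would show a slight apparent worsening. The Introduction lists the frequency and severity of exacerbation among the effects to be evaluated and expects benefit from all three regimens, so readers will probably look at within-arm change.

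**Working it through.** **Inputs from the article.** Baseline window 1 year (52 weeks); follow-up window 1 year (52 weeks, ending at week 60); enforced event-free time at least 4 weeks; 33 participants per arm.

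**Inputs assumed.** The article gives no exacerbation rate and no measure of spread between patients. I used mean rates of 0.5, 1 and 2 per patient-year, either the same for all patients (Poisson) or varying between patients (gamma with shape 1). The article states no figure for AECOPD, so there is none to reproduce.

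**Step 1: time at risk.** Before: at most 52 − 4 = 48 weeks. After: 52 weeks. Coverage is 48/52 = 92.3%.

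**Step 2: expected ratio with no change.** For a patient with constant rate λ per week, the expected counts are 48λ before and 52λ after. The after/before ratio is 52/48 = 1.083, a rise of 8.3%. Because λ cancels for each patient, differences between patients do not remove the tilt. Simulation conditional on no event in the last 4 weeks gave ratios of 1.082 to 1.085 across all the assumed rates.

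**Step 3: absolute size.** With a common Poisson rate the excess is rate × 4/52 events per patient.

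| Assumed rate per year | Expected before | Expected after | Difference |
|---|---|---|---|
| 0.5 | 0.46 | 0.50 | 0.04 |
| 1 | 0.92 | 1.00 | 0.08 |
| 2 | 1.85 | 2.00 | 0.15 |

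**Step 4: a real effect.** If the true after/before rate ratio is 0.80, the raw count ratio is 0.80 × 52/48 = 0.867. A 20% reduction appears as about 13%.

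**Step 5: effect on a paired t-test within one arm.** With n = 33, no true change and a nominal two-sided 5% level, 40,000 simulated arms per setting gave these rejection rates:

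| Assumed rate per year | Common rate | Gamma-varying rate |
|---|---|---|
| 0.5 | 5.5% | 5.3% |
| 1 | 6.1% | 5.7% |
| 2 | 7.1% | 6.6% |

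With equal windows the same test gave 4.6% to 5.1%, so the excess is at most about 2 percentage points.

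**Step 6: the randomised contrast.** Every arm has the same factor of 52/48. With a true rate ratio of 0.80 between arms, simulation returned 0.80 from the follow-up counts and 0.80 from the ratio of the two after/before ratios. An additive difference-in-difference also carries no bias: the expected baseline count is the same in randomised arms and subtracts out.

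**Step 7: a force in the other direction.** If patients tend to be enrolled after a bad year (assumed here as at least one exacerbation in the baseline year), the no-change after/before ratio falls to between 0.40 and 0.92 across the same rates. That can outweigh the 8.3%.

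**The case against.** The strongest reply is that the article never states the criticised test for this outcome. It says that exacerbations are recorded, and the paired comparison is defined around the 8 weeks of intervention, not one year against another. This stands in part. The link to AECOPD is an inference from a single general scheme with no separate method for an outcome defined as a before-and-after pair. The point is therefore conditional on that scheme being applied.

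A second reply is that the planned group-by-time and difference-in-difference analyses already deal with the problem. This stands in full for the comparison between arms, and a reader should not infer that the randomised inference is damaged.

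A reader might also infer that the before-after comparison must show a rise. The documents do not support that. A rise follows only if the underlying rate is constant. A true 20% reduction still shows as a fall, to about 0.87. Recruitment partly through "following up in the respiratory department of Shuguang Hospital" makes regression to the mean possible, though the article has no prior-exacerbation entry criterion, so its size is unknown.

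Finally, one could test all 132 patients together before and after and obtain a larger excess of rejections. The article plans comparisons within each group, so that figure has no place here.

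**Conclusion.** This is a minor point that holds conditionally. The unequal time at risk follows directly from two stated rules. It tilts a raw within-arm AECOPD ratio upward by 8.3%, given exactly 4 enforced event-free weeks and a constant rate. A longer enforced period would increase the tilt. The resulting excess of false rejections per arm is small, at about 5% to 7% against a nominal 5%, and rests on assumed rates of 0.5 to 2 per year. The practical harm is a misread before-after figure: a benefit understated by about a third (13% shown for a true 20%), or a slight apparent worsening where nothing changed. Regression to the mean may offset or reverse this, which is a further reason not to interpret within-arm change. The primary outcome, the sample size and the randomised between-arm AECOPD comparison are unaffected.

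**What to change.** 1. In the outcome definition, end the 52-week baseline exacerbation window where the 4-week stability window begins. Alternatively, keep the window and report events per week at risk, with 48 weeks as the baseline denominator.
2. In Statistical analysis, state that within-arm change in AECOPD is descriptive only.
3. State that the AECOPD conclusion rests on the between-arm comparison of follow-up counts, with the baseline count as a covariate.

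The cost is one sentence in the outcome definition and one or two in the analysis section. The baseline history is already collected, so only the recall window or the denominator changes. No visit, measurement or clinical rule is altered.
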